## Withdrawal of individual subjects

Subjects can leave the study at any time for any reason if they wish to do so without any consequences. The investigator can decide to withdraw a subject from the study for urgent medical reasons.

## Follow-up of subjects withdrawn from treatment

Patients whom have withdrawn from the study, but are still willing in participating in the follow-up will be followed according to the specifications of the patient.

# SAFETY REPORTING

## Temporary halt for reasons of subject safety

In accordance to section 10, subsection 4, of the WMO, the sponsor will suspend the study if there is sufficient ground that continuation of the study will jeopardise subject health or safety. The sponsor will notify the accredited METC without undue delay of a temporary halt including the reason for such an action. The study will be suspended pending a further positive decision by the accredited METC. The investigator will take care that all subjects are kept informed.

## AEs, SAEs and SUSARs

### Adverse events (AEs)

Adverse events are defined as any undesirable experience occurring to a subject during the study, whether or not considered related to the investigational treatment. All adverse events reported spontaneously by the subject or observed by the investiga­tor or his staff will be recorded.

### Serious adverse events (SAEs)

A serious adverse event is any untoward medical occurrence or effect that

- results in death;
- is life threatening (at the time of the event);
- requires hospitalisation or prolongation of existing inpatients’ hospitalisation;
- results in persistent or significant disability or incapacity;
- is a congenital anomaly or birth defect; or
- any other important medical event that did not result in any of the outcomes listed above due to medical or surgical intervention but could have been based upon appropriate judgement by the investigator.

An elective hospital admission will not be considered as a serious adverse event.

The sponsor will report the SAEs through the web portal *ToetsingOnline* to the accredited METC that approved the protocol, within 7 days of first knowledge for SAEs that result in death or are life threatening followed by a period of maximum of 8 days to complete the initial preliminary report. All other SAEs will be reported within a period of maximum 15 days after the sponsor has first knowledge of the serious adverse events.

## Follow-up of adverse events

All AEs will be followed until they have abated, or until a stable situation has been reached. Depending on the event, follow up may require additional tests or medical procedures as indicated, and/or referral to the general physician or a medical specialist.

SAEs need to be reported till end of study within the Netherlands, as defined in the protocol.

## Data Safety Monitoring Board (DSMB)

A DSMB will be assigned.

# STATISTICAL ANALYSIS

The clinical outcomes will be categorical or dichotomous outcomes and will be presented as absolute numbers and percentages. The chi-square test will be used for comparing categorical data among patient groups. Descriptive outcomes will be reported as median with interquartile range (IQR) or mean with standard deviation (SD) and in accordance to their distribution the Mann-Whitney-U test is used to evaluate intergroup variation.

Oncological outcome will be determined using Kaplan-Meier analyses, with comparison of relevant patient groups using the log-rank test. Predictors of main outcome parameters will be determined by selecting relevant variables based on expected association with subsequent univariable analysis. Besides stratified comparisons as described above, multivariable analysis will be performed to determine independent association of factors with a specific outcome parameter using logistic and Cox regression analyses. A p-value <0.05 will be considered to be statistically significant. All analyses will be performed with IBM SPSS statistics, version 23.00 (IBM Corp Amonk, NY, United States).

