## Hypothesis

The primary hypothesis of this study is that the implemented and standardized laparoscopic surgical technique for right-sided colon cancer will be safe without an increase in the 90 days postoperative morbidity (non-inferiority design).

The second hypothesis is that the quality of surgery, objectively assessed by competency assessment, is an important determinant for long-term clinical patient outcomes.

The clinical outcomes of the surgical technique to treat right-sided colon cancer will be improved by safely implementing a standardized method according to the latest evidence. Improvements in outcome measures that reflect the oncological quality of surgery, such as validated assessment of plane of dissection and vascular ligation, grading of the resection specimen, total lymph node count and number of resected positive lymph nodes and completeness of mesocolic excision based on postoperative CT imaging are expected. Eventually, it is hypothesized that the surrogate oncological endpoints will translate in reduction of local and distant recurrences and improved 5-year overall survival (OS) and 3-year disease free survival (DFS).

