### Secondary study parameters/endpoints

- Intraoperative complications (i.e. vascular injury, injury to other organs);
- 90-day mortality;
- Conversion;
- Operative time;
- Blood loss;
- Validated assessment of plane of dissection;
- Validated assessment of level of vascular ligation;
- Grading of the resection specimen according to Benz et al. [17];
- Total lymph node count;
- Number of resected positive lymph nodes;
- Resection margins;
- Completeness of mesocolic excision based on postoperative CT imaging;
- Locoregional recurrence;
- Distant metastasis;
- 3-year disease free survival (DFS);
- 5-year overall survival (OS);
- Long-term morbidity: incisional hernia, adhesion related small bowel obstruction, readmissions, reinterventions, anastomotic leakage.

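### Section 10 gives all categorical data an unordered chi-square test, so graded surgical-quality endpoints would be compared without using grade order, although section 4.3 expects improvement (low severity, cheap to improve)

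*Protocol*

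**What the plan says.** Section 10 gives a general rule for categories: "The chi-square test will be used for comparing categorical data among patient groups". The sentence before it classes the clinical outcomes: "The clinical outcomes will be categorical or dichotomous outcomes and will be presented as absolute numbers and percentages". A rank test is also named, but for outcomes summarised as a median or mean: "in accordance to their distribution the Mann-Whitney-U test is used to evaluate intergroup variation". No trend test or ordinal model is mentioned. Logistic and Cox regression are named for multivariable work.

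Section 8.1.2 lists three relevant secondary endpoints: a grading of the resection specimen by a cited classification, "Validated assessment of plane of dissection" and "Validated assessment of level of vascular ligation". It does not give the number of levels, their order, or a test for each endpoint.

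Section 4.3 states what is expected of them. The sentence begins "Improvements in outcome measures that reflect the oncological quality of surgery, such as validated assessment of plane of dissection and vascular ligation, grading of", continues with the specimen and lymph node measures, and ends by saying that these improvements are expected. Step 5 in section 8.2 compares the consolidation phase with pre-implementation performance on such measures (365 vs 365). Section 6.4 sets 365 control patients against 730 in the two later phases together.

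**The concern.** A specimen grade is an ordered category. A Pearson chi-square treats the grades as unordered names, so relabelling them in any order leaves the p-value unchanged. With k grades it spreads its power over k−1 degrees of freedom, including patterns of change that are neither better nor worse. Section 4.3 asks a narrower question: did quality improve? A test that uses the order puts its power on one degree of freedom in that direction.

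These endpoints are the trial's near-term evidence on oncological quality, and section 4.3 treats them as surrogates for recurrence and survival. If the grades shift moderately and evenly, the stated test is less likely to detect it. The rule also provides no effect size on the graded scale.

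**Working it through.** **Inputs from the protocol.** Group sizes are 365 vs 365 (section 8.2, step 5) and 365 vs 730 (section 6.4). The significance level is p<0.05 (section 10), taken as two-sided.

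**Assumed, because the protocol does not give them.** Number of grades (3 or 4), control distribution (equal or skewed), and effect (one common odds ratio, OR, across all grade cuts).

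**1. The plan's own figure.** It states no power for the graded endpoints, only the primary sample size. With 26% in both groups, margin 7 points, one-sided 5%, 80% power and 1:2 allocation:

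n(control) = (1.645 + 0.842)² × 0.26 × 0.74 × (1 + 1/2) / 0.07² = 364.1, so 365, with 730 in the other group and 1095 in total. This reproduces, and the present point does not touch it.

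**2. Worked case: 3 grades at 20/30/50%, OR 1.4, 365 vs 365.**
- Shifted distribution: odds at the first cut 0.25/1.4 = 0.1786, so 15.15%; at the second cut 1/1.4 = 0.7143, so 41.67%. The later phase is 15.15/26.52/58.33%.
- Chi-square: pooled proportions 0.1758, 0.2826, 0.5417. Noncentrality = 730 × (0.02424²/0.1758 + 0.01742²/0.2826 + 0.04167²/0.5417) = 5.57. On 2 df, power is 55%.
- Mann-Whitney: P(later better) + ½P(tie) = 0.3447 + 0.2008 = 0.5455. Tie-corrected null variance = 731/(12 × 365²) × (1 − 0.1869), so SE = 0.0193 and z = 0.0455/0.0193 = 2.36. Power is 65%.

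**3. Other settings at OR 1.4 (20,000 simulated trials each).**

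| Control grades | 365 vs 365: chi-square → rank | 365 vs 730: chi-square → rank |
|---|---|---|
| 3, equal | 59% → 69% | 72% → 81% |
| 3, 20/30/50% | 55% → 65% | 69% → 78% |
| 4, equal | 55% → 72% | 69% → 83% |
| 4, 10/20/30/40% | 52% → 69% | 67% → 81% |

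Applying the step 2 formulas to these four distributions at OR 1.3, 1.4 and 1.45, with both allocations, gives gains from 7 to 17 points.

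**4. Check without a grade distribution.** A noncentrality of 7.849 gives 80% power on 1 df, 71% on 2 df and 64% on 3 df.

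**5. Where the gain disappears or grows.**
- Large effect: at OR 1.75 the simulated gain for 3 or 4 grades is 2 to 4 points at 365 vs 365 and about 0 to 1 at 365 vs 730.
- Two levels: chi-square also has 1 df. For 50/50% and OR 1.4 (41.67/58.33%), noncentrality = 730 × 0.04167² × (1/0.4583 + 1/0.5417) = 5.10, and both tests have about 62% power.
- Five equal grades, OR 1.4: the gain is 19 to 22 points.

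**6. Where it reverses.** For 20/30/50% changing to 13/37/50% at 365 vs 365:
- Chi-square: 730 × (0.035²/0.165 + 0.035²/0.335) = 8.09, power 72% (simulation 72 to 73%).
- Mann-Whitney: 0.324 + 0.1935 = 0.5175, SE 0.0195, z = 0.90, power 15%.

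**The case against.** The strongest reply is that section 10 is a general paragraph. It assigns no test to any of these endpoints by name, and the mapping may sit in an analysis plan that is not shown. A grade could be summarised as a median and tested by Mann-Whitney within the existing text. This tempers the point but does not remove it: the protocol does state a rule for categorical data, without an exception, and an analysis plan that followed it literally would inherit the unordered test.

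Four stronger readings are tempting, and the document does not support them.
- A reader might infer that all three endpoints are ordered. Only the specimen endpoint is called a grading; no scale is given for plane of dissection or level of ligation.
- A reader might take 7 to 17 points as a property of this plan. It follows from assumed grades, distributions and effects.
- A reader might conclude that the direction of change would be unknown. The p-value carries no direction, but section 10 has outcomes presented as counts and percentages, which would show it.
- A reader might call the test wrong. Simulated type I error is about 5% for both tests.

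The reversal in step 6 also stands. If standardisation removes the worst resections without raising the share in the top grade, that is a real improvement, and a rank test may miss it.

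**Conclusion.** The point holds as a low-severity, inexpensive improvement on secondary endpoints. The stated rule leads on its plain reading to a valid test that is not matched to the directional hypothesis. This is clear for the specimen grade and conditional for the other two endpoints. The size of the gain in the working depends on a uniform shift of moderate effect over 3 or 4 grades, none of which the protocol specifies. An ordered test is the better default because section 4.3 hypothesises general improvement, not because it wins under every pattern of change. Non-inferiority on 90-day morbidity and the 365 + 730 sample size are not affected.

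**What to change.** In section 10:
- Limit the chi-square test to dichotomous and unordered categorical outcomes.
- For any endpoint on an ordered scale, use the tie-corrected Mann-Whitney test already named in the plan, or the linear-by-linear trend test.
- Report a common odds ratio with 95% CI from proportional-odds regression.
- Always show the full grade table by phase.

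Say in the same place which of the three endpoints are on an ordered scale, and settle this before the grades are compared, so that the choice of test does not depend on the results.

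The cost is one or two sentences, with no extra patients or data. The downside to state openly is lower sensitivity to non-uniform shifts; the full grade table lets a reader see such a pattern.

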# STUDY DESIGN

The design of this trial is a multicenter prospective interventional sequential cohort study with a transition period in which implementation of the standardized technique is performed in the same centers after education and hands on training. Proctoring of the new technique will be provided during implementation. The second data evaluation of the clinical and oncological outcomes of the consecutive patient group will be collected in the group of patients after proctoring is finished, the so called consolidation phase. This study is primarily designed as a non-inferiority trial, based on short-term postoperative complications, with the aim of ultimate improvement of long-term oncological outcome. The accrual of both the control patients and the patients after implementation will be within the national Prospective Dutch ColoRectal Cancer cohort (PLCRC) with additional video analysis and image collection with additional informed consent. The primary endpoint is safety during implementation of a new technique. This is measured by 90-day morbidity with the Clavien-Dindo classification [15]. The assumption is that the perioperative morbidity (26% 30-day overall postoperative complication rate; as earlier published based on the DCRA database [16]) will not be increased by implementation of the new standardized technique with a non-inferiority margin of 7%, therefore not exceeding 33%.

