## Sample size calculation

Sample size calculation is performed with the aim to demonstrate safety with non-inferiority for the primary endpoint overall 90-day morbidity. If there is truly no difference between the standard and experimental treatment, then 1095 patients (365 patient in each of the three groups) are required to be 80% sure that the lower limit of a one-sided 95% confidence interval (or equivalently a 90% two-sided confidence interval) will be above the non-inferiority limit of 7%. Therefore, in the one group 365 patients will be included (control group) and in the other group 730 patients will be included (implementation and consolidation phase together).

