# METHODS

## Study parameters/endpoints

### Main study parameter/endpoint

The primary endpoint is the 90-day morbidity with Clavien-Dindo classification.

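### The Statistical Analysis section tests 90-day morbidity for equality by chi-square and does not carry forward the non-inferiority criterion that sizes the trial, which section 6.4 itself states in the wrong direction

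*Protocol*

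**What the plan says.** Four parts of the protocol bear on this.

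- **Question.** Section 5 states: "This study is primarily designed as a non-inferiority trial, based on short-term postoperative complications". Section 4.3 words the primary hypothesis the same way.
- **Endpoint.** Section 8.1.1: "The primary endpoint is the 90-day morbidity with Clavien-Dindo classification".
- **Criterion.** Section 5 starts from a "26% 30-day overall postoperative complication rate" and allows an increase "with a non-inferiority margin of 7%, therefore not exceeding 33" per cent. Section 6.4 opens with "Sample size calculation is performed with the aim to demonstrate safety with non-inferiority for the primary endpoint overall 90-day morbidity". It then gives 365 controls and 730 patients in the implementation and consolidation phases together, 80% power, and a one-sided 95% (two-sided 90%) confidence limit set against 7%. As printed, it is the lower limit that must lie above 7%.
- **Analysis.** Section 10 describes the clinical outcomes as categorical or dichotomous and then says "The chi-square test will be used for comparing categorical data among patient groups". Its decision level is "A p-value <0.05 will be considered to be statistically significant". It also provides for logistic and Cox regression to find predictors and independent associations. It does not mention non-inferiority, the margin, a confidence interval for the difference, or a one-sided level, and it does not set the primary endpoint apart.

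**The concern.** Overall 90-day morbidity is a yes/no outcome, so the general chi-square sentence covers it. That test has a null hypothesis of zero difference. The trial's question has a null hypothesis of an increase of at least 7 points. Failing to reject the first says nothing about the second: a non-significant result may only mean that the data are too few. The error rate and power in section 6.4 belong to the interval rule and do not carry over to the chi-square.

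The two sections therefore point to different tests of the primary endpoint, and neither gives a decision rule that can be applied as printed. At stake is the main safety conclusion about a surgical technique being introduced in more than 40 centres.

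**Working it through.** **Inputs.** Control rate 0.26, margin 0.07 and ceiling 0.33 (section 5); no true difference, one-sided 5%, 80% power, 365 vs 730 (section 6.4); chi-square at p<0.05 (section 10), taken as the usual uncorrected two-group test. Differences are new minus control.

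**1. Reproduce the sample size.** With allocation 1:2 and unpooled variance,

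n(control) = (1.645 + 0.8416)² × 0.26 × 0.74 × (1 + 1/2) / 0.07² = 6.183 × 0.1924 × 1.5 / 0.0049 ≈ 364.2, rounded up to 365.

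This gives 365 + 730 = 1095, exactly as stated. The number therefore rests on a confidence limit compared with the margin, which section 10 does not contain.

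**2. Direction of the criterion in section 6.4.** For new minus control, a lower limit above +7 would show that the new technique is worse by more than the margin. For control minus new, a lower limit above +7 would show that it is better by more than 7 points. Neither is non-inferiority. The correct rule is an upper limit below +7 for new minus control or, equivalently, a lower limit above −7 for control minus new.

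**3. True rate at the ceiling (33%), 365 vs 730, normal approximation.**
- Standard error of the difference: √(0.26×0.74/365 + 0.33×0.67/730) = 0.0288.
- Pooled rate 0.3067; standard error used by the chi-square: 0.0296; smallest significant difference: 1.96 × 0.0296 = 0.0579.
- P(non-significant) = Φ((0.0579 − 0.07)/0.0288) = 0.338.
- P(interval rule passes) = Φ((0.07 − 0.07)/0.0288 − 1.645) = 0.050.

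**4. True rate 31%, 365 vs 730.** The standard error is 0.0286 and the smallest significant difference 0.0572.
- P(non-significant) = Φ((0.0572 − 0.05)/0.0286) = 0.599.
- P(interval rule passes) = Φ((0.07 − 0.05)/0.0286 − 1.645) = 0.172.

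**5. Exact binomial enumeration of both rules** (control 26%, Wald 90% interval):

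| Sizes | True new rate | Chi-square p≥0.05 | Interval rule passes |
|---|---|---|---|
| 365 vs 730 | 26% | 95.0% | 80.6% |
| 365 vs 730 | 31% | 59.7% | 16.8% |
| 365 vs 730 | 33% | 33.6% | 4.8% |
| 365 vs 365 | 33% | 45.4% | 5.0% |
| 183 vs 365 | 33% | 61.2% | 4.7% |
| 100 vs 200 | 33% | 76.8% | 4.7% |

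With no true difference at 365 vs 730, 17.0% of trials are non-significant yet do not meet the margin. At a true 33%, non-significance becomes more frequent as the sample shrinks, while the interval rule stays near 5%.

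**6. One data set, two answers.** Take 95/365 (26.0%) vs 226/730 (31.0%). The difference is 4.9 points and the chi-square p is 0.091, so not significant. The upper 90% limit is 0.0493 + 1.645 × 0.0286 = 0.096, or +9.6 points, so non-inferiority is not shown.

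**The case against.** The best defence is that the protocol does contain the criterion. Section 6.4 ties the primary endpoint to a confidence limit and a margin, section 5 repeats the margin, and section 10 is general text by data type that never names the primary endpoint. A specific statement may be taken to govern a general one, and the interval method could be left to a statistical analysis plan.

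Much of this stands. A reader might infer that the trial has no non-inferiority criterion at all; sections 5 and 6.4 rule that out. The absence of an interval method from section 10 would not be a finding on its own. What remains is that section 10 states a method that covers the primary endpoint and tests a different hypothesis, while the section that would have to override it is worded in the wrong direction.

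Four stronger readings are not supported:

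- *That the protocol equates non-significance with safety.* It nowhere says so. The percentages for chi-square are conditional on that reading. It is a real risk only because section 10 offers no other rule.
- *That the two sections set openly conflicting error rates.* Section 10 gives no sidedness for its 0.05. The chi-square implies a null hypothesis of equality, but the threshold sentence alone would also fit a one-sided 5% test.
- *That chi-square is the only method offered for this endpoint.* Logistic regression is also listed, though it is not tied to the margin either.
- *That a significantly worse result could still meet the criterion.* At the planned size this practically never happens. With 95/365 vs 232/730 the difference only just reaches p = 0.0499, and the upper 90% limit is already +10.5 points.

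**Conclusion.** The point holds as an internal inconsistency about the primary analysis. Section 10 applies a test of equality to an endpoint whose criterion in section 6.4 is a confidence limit against a 7-point margin, and section 6.4 prints that criterion the wrong way round. The design figures themselves are coherent: margin, level, power and 1095 patients agree exactly.

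If non-significance were taken as no increase, an increase to the protocol's own ceiling would pass in about 34% of trials at 365 vs 730 (45% at 365 vs 365), against about 5% under the interval rule. At a true 31% it would pass in 60% against 17% (365 vs 730).

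These figures assume 26% control morbidity, which the protocol takes from a 30-day rate for a 90-day endpoint. They also assume independent patients and an uncorrected two-group chi-square. Because the primary conclusion depends on it, this should be settled before the analysis.

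**What to change.** In section 10, add a paragraph for the primary endpoint along these lines: *The primary analysis is the risk difference in 90-day morbidity, standardised technique (implementation plus consolidation phases, n=730) minus control (n=365), with a two-sided 90% confidence interval. Non-inferiority is concluded only if the upper limit is below +7 percentage points.*

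Reword section 6.4 to the same limit and direction. Restrict chi-square and the p<0.05 threshold to the secondary comparisons.

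The comparison needs to be named because section 6.4 sizes the pooled 730, whereas section 5 places the second data evaluation in the consolidation phase. With consolidation patients alone (365 vs 365), power for non-inferiority would be 69.5%, not 80%.

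The cost is one paragraph and one corrected sentence in a protocol amendment, with any statistical analysis plan aligned to it. No extra patients or data are needed.

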# APPENDIX

## Study flowsheet showing patient pathway and CRF completion times

Patient pathway: Suggested CRF completion times:

Decision to operate

CRF 1: Registration form

CRF 2: Patient characteristics

CRF 3: Preoperative CT-imaging

CRF 4: Preoperative tumor characteristics

CRF 5: Video and surgical details

CRF 6: Specimen

CRF 7: Pathology

CRF 8: Follow-up 3 months

CRF 9: Follow-up 12 months

CRF 10: 1 year postoperative CT-imaging

CRF 11: Follow-up 36 months

CRF 12: Follow-up 60 months

CRF 7-12

CRF 4-6

CRF 1-3

Patient discharged

Operation

Pre-operative assessment clinic

Routine outpatient review

(around 4-6 weeks)

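### Kaplan-Meier is assigned to all oncological outcomes, including locoregional recurrence and distant metastasis, where censoring deaths would modestly overstate the absolute incidence (minor)

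*Protocol*

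**What the plan says.** Section 10 of the protocol (Statistical Analysis) gives one rule for long-term cancer outcomes: "Oncological outcome will be determined using Kaplan-Meier analyses, with comparison of relevant patient groups using the log-rank test". It adds that "multivariable analysis will be performed to determine independent association of factors with a specific outcome parameter using logistic and Cox regression analyses". It does not list the endpoints that the Kaplan-Meier sentence covers, does not say how a death without recurrence is handled, and names no competing-risks method.

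Section 8.1.2 lists "Locoregional recurrence" and "Distant metastasis" as secondary endpoints, separate from 3-year DFS and 5-year OS. The Hypothesis section (4.3) names fewer local and distant recurrences, next to better OS and DFS, as the expected eventual gain of the standardized technique. The flowsheet in the appendix ends with "CRF 12: Follow-up 60 months".

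**The concern.** Kaplan-Meier suits OS, and it suits DFS when death counts as an event. Recurrence alone is different: a patient who has died without recurrence can no longer recur. Kaplan-Meier for recurrence ordinarily treats that patient as censored, that is, as someone who could still recur later at the same rate as the survivors. One minus Kaplan-Meier then estimates the risk of recurrence in a hypothetical setting without other deaths, and it exceeds the proportion of patients who actually recur whenever such deaths occur.

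Some deaths of this kind are to be expected. Follow-up runs to 60 months, the inclusion criteria set no upper age limit, and 90-day mortality is itself an endpoint. At stake are the absolute rates of locoregional recurrence and distant metastasis reported for each phase, which bear on a gain that the protocol expects.

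**Working it through.** **The plan's own figures.** The protocol gives no rate for recurrence or for death without recurrence, so there is no figure on this point to reproduce. Its only sample size concerns 90-day morbidity. With 26% in both groups, a margin of 7 points, one-sided 5%, 80% power and 1:2 allocation:

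n(control) = 0.26 × 0.74 × (1 + 1/2) × (1.645 + 0.842)² / 0.07² ≈ 364.1, rounded up to 365.

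That gives 365 + 730 = 1095, as stated in section 6.4. It has no bearing on the recurrence endpoints.

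**Inputs for the check (all assumed).**
- r: recurrence at 5 years by one minus Kaplan-Meier with deaths censored, 3% to 20%.
- d: net probability of death without recurrence by 5 years, 5% to 25%.
- Constant cause-specific hazards.

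**Formulas.**
- Recurrence hazard h1 = −ln(1 − r)/5.
- Death hazard h2 = −ln(1 − d)/5.
- Cumulative incidence CIF = h1/(h1 + h2) × [1 − exp(−5(h1 + h2))].

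**One case in full, r = 10% and d = 15%.**
- 5·h1 = 0.1054 and 5·h2 = 0.1625, sum 0.2679.
- h1/(h1 + h2) = 0.1054/0.2679 = 0.3933.
- 1 − exp(−0.2679) = 1 − 0.90 × 0.85 = 0.235.
- CIF = 0.3933 × 0.235 = 0.0924.
- Overstatement: 10% − 9.24% = 0.76 points; 10/9.24 − 1 ≈ 8%.

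**Cumulative incidence over the range.**

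| 1 − Kaplan-Meier | d = 5% | d = 15% | d = 25% |
|---|---|---|---|
| 3% | 2.92% | 2.77% | 2.61% |
| 5% | 4.88% | 4.62% | 4.35% |
| 10% | 9.75% | 9.24% | 8.71% |
| 15% | 14.63% | 13.88% | 13.09% |
| 20% | 19.51% | 18.52% | 17.47% |

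The smallest gap is 3% − 2.92% = 0.08 points and the largest is 20% − 17.47% = 2.53 points. The relative overstatement depends almost only on d: about 2.5% at d = 5%, 8% at d = 15% and 15% at d = 25%.

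**Effect on the comparison between phases.** In this model one minus Kaplan-Meier equals 1 − exp(−5·h1), which contains no death hazard. The CIF does contain it. With the recurrence hazard held at the value that gives r = 10%, the CIF is 9.75% at d = 5% and 8.71% at d = 25%, a difference of 1.04 points with no change in the recurrence hazard. So it is the cumulative incidence, not the log-rank or Cox comparison with deaths censored, that moves with competing mortality.

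**The case against.** **The sentence does not name recurrence and states no censoring rule.** This is correct. A recurrence-free survival endpoint that counts death as an event would fit the same words, and so would a yes/no analysis by logistic regression. Event and censoring rules for secondary endpoints are also commonly left to the SAP, which is not shown. What stands is that the censoring of deaths is inferred, so the conclusion is conditional. The choice of estimator, however, is made in the protocol and without exception. No recurrence-free composite is named, and a composite of any recurrence or death would largely duplicate DFS.

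**Step 5 of the Study procedures (section 8.2) names only 3-year DFS and 5-year OS for the long-term comparison with the pre-implementation phase.** This supports a narrower reading, under which Kaplan-Meier is used only where it fits. It does not take the recurrence endpoints out of the general sentence in section 10, and sections 4.3 and 8.1.2 treat them as oncological results in their own right.

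**A reader might infer that the phase comparison is distorted by non-cancer or postoperative mortality.** The documents and the arithmetic do not support this. Log-rank and Cox with deaths censored compare the cause-specific hazard of recurrence, a valid target and a relevant one for a surgical technique. The protocol already plans both methods.

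**The size is small.** With 365 patients, an observed 10% has a 95% half-width of 1.96 × √(0.10 × 0.90/365) ≈ 3.1 points, against a gap of 0.25 to 1.29 points at that rate. The exclusion of M1, cT4b, ASA 4 and emergency cases also makes the low end of the mortality range relevant. This stands and sets the severity. The gap is nevertheless systematic and does not shrink with more patients.

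**Conclusion.** The point holds as a minor one. On its plain reading, section 10 applies Kaplan-Meier to locoregional recurrence and distant metastasis. If deaths without recurrence are censored, the absolute rates are overstated by about 0.1 to 2.5 percentage points (2.5% to 15% relative). The direction is certain under that censoring rule. The size rests on assumed rates and constant hazards, because the protocol gives none.

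It would go too far to say that the plan expressly censors these deaths, that the Kaplan-Meier sentence is wrong as a whole, or that the tests between phases are invalid. The effect is confined to absolute estimates of two secondary endpoints. The primary endpoint, the sample size, OS, and DFS with death as an event are untouched.

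**What to change.** In section 10, replace the general sentence with three statements:
- OS and DFS are estimated by Kaplan-Meier, with death counted as an event in DFS.
- Locoregional recurrence and distant metastasis are each estimated by cumulative incidence (Aalen-Johansen), with death without that event as the competing event.
- The log-rank and Cox comparisons of these two endpoints are kept, with deaths censored, and are labelled as comparisons of the cause-specific hazard.

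Because cumulative incidence moves with competing mortality, the curves for death without recurrence should be shown next to it, so that a difference between phases can be read correctly. If a composite of recurrence or death was intended instead, the protocol should name it as such.

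The cost is a few lines of text and a small program, possibly outside the named package. No new data are needed, because deaths must already be recorded for OS and DFS.
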